### Secondary outcomes

Most secondary outcome measures will be applied at distinct time points at the beginning and end of each study phase to assess pre- to post-changes for each study phase as well as at the follow up (see Fig. 1 for details). Muscle strength and motor control abilities of the “unwanted” movement will be assessed at similar time points as the primary outcome.

#### Clinical measures of SVMC

We will conduct the SCALE [27] or the SCUES [28], depending on whether a lower or upper extremity target joint will be trained. These clinical assessments require the participant to perform reciprocal movements at various joints: hip flexion/extension, knee flexion/extension, ankle dorsiflexion/plantarflexion and eversion/inversion, and toes flexion/extension for the lower extremities, and shoulder abduction/adduction, elbow flexion/extension, forearm pronation/supination, wrist flexion/extension, and finger flexion/extension for the upper extremities. The assessment will be videotaped for blinded evaluation. SVMC is scored on a three (SCALE) or four-point (SCUES) scale for each movement. Variables of interest are the score of the target joint, the summed score of the target joint side, and the total score. These two clinical tools have been shown to be valid and reliable to assess selective control of the lower/upper extremities in our target population [27–30].

#### Muscle strength

As strength was shown to be related to SVMC [31], we will assess the muscle strength of the target joint with dynamometry. We will use a hand-held dynamometer (microFET 2, Hoggan Scientific, Salt Lake City) to measure the force produced. We will conduct the test in standardized positions (see Additional file 1) to increase reliability and use the average value received from three repetitions allowing 30 to 60s rest in between trials. Upon the go-signal, participants should push as hard as they can against the dynamometer for 5 s while the assessor counts back the seconds.

#### Cortical excitability

We will use a standardized protocol to determine the motor threshold and the latency and amplitude of the motor evoked potential (MEP). A single-pulse TMS will be performed using a MagPro X100 Magnetic Stimulator (MagVenture A/S, Farum, Denmark) in combination with a Keypoint G3 Workstation (DANTEC Medical A/S, Skovlunde, Denmark). Electrodes will be placed on the muscle belly of the muscle that is also the target muscle group of the intervention. For all measurements, a MFC-B65 Butterfly figure-of-eight coil will be used to stimulate the primary motor cortex. If a lower extremity muscle group is trained, the coil will be positioned just lateral to the midline, close to Cz (Vertex), contralateral to the target muscle [32]. If an upper limb muscle group is trained, the coil will be positioned close to C3h (left) or C4h (right) [33]. The coil will be moved in small increments to find the location with the largest response (i.e., hot spot). Participants will wear a bathing cap and this location will be marked on it. We will use a biphasic single-pulse stimulus, as these are more effective than monophasic pulses, with a pulse duration of 200 μs. The stimulus threshold will be expressed as the percentage of maximal stimulator output that evokes an MEP amplitude of at least 50 μV in approximately 50% of 10 consecutive stimuli (i.e., motor threshold). The stimulation intensity will be set at 1.2 times the motor threshold. We will perform five stimulation repetitions to determine the parameters latency and amplitude of the MEP in the averaged signal. On the second and third TMS test occasions, the procedure will be repeated. Again the stimulation threshold is determined and noted for comparison. Independent from the new threshold level, the stimulations to determine MEP latency and amplitude are performed at the same level of stimulator output as performed during the first measurement. TMS measurements will be conducted in separate appointments.

#### Motor control of the joint showing involuntary co-movements or co-activations

We want to explore whether our training intervention also affects movement control of the joint that is showing involuntary muscle activations/movements. Our exploratory hypothesis is that learning to inhibit muscle activity/movement by means of the SVMC game could lead to improved control of that muscle/joint. To study this, participants will perform the mini-assessment with the joint that will become trained to stay “inactive” during the game. For this research question, we will only evaluate the accuracy of the movement (i.e., no feedback on involuntary movements for this test). Repeated testing will be conducted during the baseline phase and at the end of the intervention to keep the burden for the participants low. Procedures will be the same as described for the primary outcome, including the try-out phase.

#### Functional independence

To assess the children’s functional independence in daily life activities, we will use the domains mobility (for the lower extremities) and self-care (for the upper extremities, excluding bladder and bowel items) of the Functional Independence Measure for children (WeeFIM®). The WeeFIM® measures activity on the performance level and rates independence on a scale from 1 (total assistance needed) to 7 (complete independence, performs task timely and safely) [34]. In the Swiss Children’s Rehab, it is assessed by trained and certified nurses on a regular basis.

#### Potentially confounding ongoing therapies

We will record concomitant regular therapies the participants attend over the course of the study between the first and last mini-assessment session of each phase. The corresponding therapist(s) will be asked whether improving SVMC was part of their therapy sessions.

#### Measures describing the intervention

Intervention sessions will be described by the active training time when the participant was actually playing, excluding the setup and any rests taken between levels, which will be automatically logged. We will further record any events during the training, like software errors or modifications to the setup.

### Sample size calculation

We approximate the number of participants needed with calculations based on a general linear model and later correct for the fact that measurements from one participant are not independent observations (clustering). In a general linear model, 78.4 observations are sufficient to detect a medium to large effect (r = 0.4, R^2^ = 0.16) [35] with a power of 90%, α = 0.05 and 3 degrees of freedom for the numerator (two fixed effects and one random effect), calculated with the pwr.f2.test function of the R package ‘pwr’ [36].

The correction, also called the design effect, accounts for the degree of variance inflation that attributes to clustering (several measurements from one participant). The design effect equals 1 + (*m* − 1) ∗ *ρ*, where m is the number of data points per cluster (i.e., participant) and ρ is the intraclass correlation within clusters [37]. We estimate ρ = 0.18 for the percentage score combining the accuracy and involuntary movement outcome based on unpublished data from our pilot study with six participants. In this trial, the mini-assessment was conducted three times before the first training and once before and after the following 4 training sessions. According to the formula, the design effect thus equals 3.80, assuming that m = 16.5 data points will be recorded for a person on average (i.e., expected value for randomly between 5 and 8 assessments in the baseline phase and 10 during the intervention).

Multiplying 78.4 with the design effect yields the total number of observations needed, which is then divided by 16.5 observations per person. Allowing a dropout rate of 10%, we will need 20 participants.

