### Statistics

#### Primary research aim

The statistical analyses will be carried out with R statistical package [38]. The primary analysis of the efficacy will include a (hierarchical) mixed-effect model for the variable combining the accuracy and involuntary movement outcome. On a first level, the scores of the individual participant will be modeled by a set of predefined predictors, i.e., the session number (time), and the interaction of the session with the treatment phase. On a second level, the model parameter estimates will be allowed to vary between participants (random effects). We will account for the serial dependency of the data with a first-order autoregressive correlation structure of within-subject errors. The parameter of primary interest will be the interaction of time with the treatment phase, hence the change in trend when the intervention is introduced. Depending on the distribution and shape of the trend of the data, linear or additive mixed models will be used. Additionally, the same analysis will be conducted for the accuracy and involuntary movement outcome separately to investigate whether they show comparable effects.

For a patient-level analysis, a similar regression model will also be run for each individual participant.

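### The stated 90% power belongs to a 3-df whole-model test, so 90% power is not shown for the single session-by-phase coefficient that is primary

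*Protocol article*

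**What the plan says.** The protocol article's Sample size calculation section states that "78.4 observations are sufficient to detect a medium to large effect (r = 0.4, R^2^ = 0.16"), "with a power of 90%, α = 0.05" and "3 degrees of freedom for the numerator (two fixed effects and one random effect"). It then applies a correction that "accounts for the degree of variance inflation that attributes to clustering", namely 1 + (m − 1)ρ, "where m is the number of data points per cluster (i.e., participant) and ρ is the intraclass correlation within clusters". With ρ = 0.18 from pilot data and m = 16.5 the stated design effect is 3.80. Dividing by 16.5 and allowing 10% dropout gives 20 participants. The section calls the whole calculation an approximation.

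The Primary research aim section describes a different test. The predictors are session number and its interaction with treatment phase. "The parameter of primary interest will be the interaction of time with the treatment phase". In addition, "the model parameter estimates will be allowed to vary between participants (random effects"), and within-participant errors are first-order autoregressive.

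**The concern.** The power figure and the primary test do not refer to the same hypothesis, in three respects.

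- **Test.** The 3-df calculation concerns whether the predictors jointly explain anything. A steady practice or recovery trend with no treatment effect would count towards that R². The primary question is whether one coefficient differs from zero.
- **Degrees of freedom.** A random effect is a variance component. It does not add a numerator degree of freedom to a test of fixed effects.
- **Variance correction.** The factor 1 + (m − 1)ρ inflates the variance of comparisons between participants. The session-by-phase contrast lies within participants. Its precision depends on how much the slope change varies between participants and on autocorrelation. The analysis model contains both and the calculation contains neither.

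At stake is how the result will be read. A null finding would be judged against a 90% claim that was never derived for the parameter tested.

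**Working it through.** **1. Reproduce the plan's figure.** Inputs from the Sample size calculation section: α = 0.05, power 0.90, u = 3, R² = 0.16, ρ = 0.18, m = 16.5, dropout 10%.

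- f² = 0.16/0.84 = 0.1905. The noncentral F with λ = f²(u + v + 1) gives v = 74.43, so N = 74.43 + 3 + 1 = 78.43 (stated 78.4).
- Design effect = 1 + 15.5 × 0.18 = 3.79 (stated 3.80, consistent with an unrounded ρ).
- 78.4 × 3.80 / 16.5 = 18.06 participants; 18.06/0.9 = 20.07, or 18.06 × 1.1 = 19.87. The stated 20 is reproduced.

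**2. Change only the numerator df.** With u = 1 and all of R² = 0.16 given to the interaction, N = 57.15 observations. Keeping the plan's design effect, power is 96.4% with 18 completers and 97.8% with 20. If the interaction carries 75% of that R², power is 90.2% and 93.1%; at 50% it is 75.7% and 80.2%. The answer therefore turns on a split of R² that the protocol does not give.

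**3. Why the design effect does not fit.** For a contrast whose weights sum to zero within a participant, a shared random intercept cancels. Under a random intercept alone, multiplying by 3.80 is therefore conservative. If the slope change has between-participant SD τ, its estimated mean carries an extra variance of about τ²/n, which more sessions per participant cannot reduce. Neither τ nor an AR(1) value is stated.

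**4. How much of a whole-model R² belongs to the interaction.** I used baselines of 5, 6, 7 and 8 sessions in equal numbers, each followed by 10 intervention sessions, and two codings, because the protocol does not say which applies:

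| Coding of the interaction | Correlation with session (r) | Partial f² = 0.1905 × (1 − r²) |
|---|---|---|
| Sessions since intervention start | 0.932 | 0.025 |
| Plain product, session × phase | 0.954 | 0.017 |

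If 0.16 is whole-model R² and all of it comes from a slope change, most of it is shared with the time term.

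**5. Power for the coefficient in the mixed model.** Var(β̂) = [Σ X′V⁻¹X]⁻¹, with fixed effects intercept, session and interaction. V is made up of a random intercept, AR(1) errors and a random slope change. Total variance excluding the slope change is set to 1 (0.18 between participants, 0.82 within). The test is a two-sided 5% noncentral t on n − 1 df. AR(1) = 0.3 and slope-change SD equal to its mean are my assumptions.

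Reading A, 0.16 as whole-model R² from a slope change:

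| Scenario | 18 completers | 20 completers |
|---|---|---|
| No AR, no slope heterogeneity | 63–73% | 68–78% |
| AR(1) = 0.3 | about 56% | about 61% |
| AR(1) = 0.3, slope-change SD = mean | about 45% | 49–51% |

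The ranges span the two codings. Reading B, 0.16 as the interaction's own partial R², gives about 90% to nearly 100% in the same scenarios. It implies a slope change of about 0.23 (plain product) to 0.34 (sessions since start) SD per session, that is 2.3 to 3.4 SD over ten sessions.

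**The case against.** The strongest reply is that two of the mismatches favour the plan. At the same R², 1 df needs 57 observations rather than 78.4, and the 3.80 multiplier is conservative for a within-participant contrast under a random intercept. On that footing power exceeds 90%. The section also openly calls itself an approximation, and the analysis model is unaffected, so estimates, intervals and type I error do not change.

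Much of this stands. A reader might infer from the mismatch that 20 participants cannot deliver 90% power. The documents do not support that: they fix neither the split of R², nor the AR(1) value, nor the slope-change SD, and under Reading B 90% is reached. Nor should the partial f² from step 4 be combined with 78.4 effective observations to give a very low power. That would rely on the same multiplier that step 3 rejects.

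What does not stand is the defence of the 90% figure itself. Reading B conflicts with the u = 3 that the plan used, since a single coefficient requires u = 1. It also needs a large slope change that the protocol neither states nor justifies.

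**Conclusion.** The point holds as a mismatch between the power statement and the primary test. The 90% was computed for a 3-df joint test with a miscounted random effect and a between-participant correction. It was not computed for the session-by-phase coefficient, so 90% power for the primary parameter is not shown.

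The size of any shortfall is open. Across the scenarios above, power with 18 to 20 completers runs from about 45% to nearly 100%. Every figure rests on assumed effect size, coding, autocorrelation and slope heterogeneity, and on a linear model with a 1-df interaction. A claim that the trial is underpowered would go further than the documents allow.

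**What to change.** Replace the 90% statement with simulated power, or the minimum detectable slope change, for the phase-by-time coefficient in the planned mixed model. Use 18 and 20 participants with 5–8 baseline and 10 intervention sessions. State the coding of the interaction, the assumed slope change, the residual SD, the AR(1) value and the random-slope SD. Take these from the pilot where possible and show results over a range. Drop the 3-df test and the 3.80 multiplier as justification.

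The cost is a short simulation and a reworded section. N stays at 20 and the analysis model does not change. The drawback is that the stated power may become less favourable.

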### Statistics

#### Primary research aim

The statistical analyses will be carried out with R statistical package [38]. The primary analysis of the efficacy will include a (hierarchical) mixed-effect model for the variable combining the accuracy and involuntary movement outcome. On a first level, the scores of the individual participant will be modeled by a set of predefined predictors, i.e., the session number (time), and the interaction of the session with the treatment phase. On a second level, the model parameter estimates will be allowed to vary between participants (random effects). We will account for the serial dependency of the data with a first-order autoregressive correlation structure of within-subject errors. The parameter of primary interest will be the interaction of time with the treatment phase, hence the change in trend when the intervention is introduced. Depending on the distribution and shape of the trend of the data, linear or additive mixed models will be used. Additionally, the same analysis will be conducted for the accuracy and involuntary movement outcome separately to investigate whether they show comparable effects.

For a patient-level analysis, a similar regression model will also be run for each individual participant.

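### The primary model lists no phase term, so with a running session number the coefficient named as the change in trend mixes level change and slope change

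*Protocol article*

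**What the plan says.** Under Statistics, Primary research aim, the individual scores are modelled by predefined predictors, given as a closed list: "the session number (time), and the interaction of the session with the treatment phase". Model parameters may vary between participants, with a "first-order autoregressive correlation structure of within-subject errors". The primary parameter is then named and interpreted: "The parameter of primary interest will be the interaction of time with the treatment phase, hence the change in trend when the intervention is introduced". The same section adds: "Depending on the distribution and shape of the trend of the data, linear or additive mixed models will be used".

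The Sample size calculation counts "two fixed effects and one random effect", so it has no separate phase effect either. Nothing in the article centres session or restarts it at the phase change.

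Under Study design, the baseline has 5 to 8 assessment sessions, at random, and the intervention has 10. Under Primary outcome, the mini-assessment directly follows training in the intervention phase, but follows a 75 s try-out in the baseline phase.

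**The concern.** Write t for the running session number and P for phase (0 baseline, 1 intervention). The listed model is score = a + b·t + c·t·P. The two lines coincide at t = 0, several sessions before the intervention can start. The departure from the baseline line is therefore c·t, which already has size c·(number of baseline sessions + 1) at the first intervention session. So c can be read as a slope change only if a jump of exactly that size also occurs.

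This coefficient is the trial's primary test. A gradual training effect that begins at the phase change would be badly understated, and a step at the phase change would be reported as a change in trend. A step is plausible here because the measurement conditions differ between phases: warm-up, practice or fatigue from the session just completed could shift the score in either direction. The same terms or coefficient are reused for the two component outcomes, the participant-level regressions, the moderator analyses, the strength model and the correlation of strength with SVMC changes.

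**Working it through.** **The plan's own figure.** The inputs are R² = 0.16, so f² = 0.16/0.84 = 0.1905, with 3 numerator df, 90% power and α = 0.05. The noncentral F gives 78.4 observations, as stated. The design effect is 1 + 15.5 × 0.18 = 3.79 (stated 3.80). Then 78.4 × 3.79 / 16.5 = 18.0 participants, and 18.0 / 0.9 = 20.0. The stated 20 reproduces.

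**The forced jump.** The first intervention session is t = 6 to 9 and the last is t = 15 to 18. The model departs from the baseline line by 6c to 9c at the first and 15c to 18c at the last. It thus requires 6/15 = 40% to 9/18 = 50% of the final effect to be present at the first session. A true slope change without a jump has 1/10 = 10% of it there.

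**Size.** Known mean curves were projected by generalised least squares onto the listed model and onto the model with a phase term.
- From the article: baseline of 5 to 8 sessions, 10 intervention sessions, ICC 0.18, and 18 completers (20 less 10%).
- Assumed, because the article gives no value: total SD of 10 points, AR(1) of 0 or 0.3, the effect sizes, and a random intercept only. Tests use t with 17 df. Lower scores are better.

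| Truth | Listed model, running session: estimate | Significant | With phase term: estimate | Significant |
|---|---|---|---|---|
| Slope change -1, no jump | -0.22 to -0.24 | 10-12% | -1.00 | 38-52% |
| Level shift -5, no slope change | -0.58 to -0.60 | 44-47% | 0.00 | 5% |
| Level shift -10, no slope change | -1.16 to -1.20 | 95-96% | 0.00 | 5% |
| No effect | 0.00 | 5% | 0.00 | 5% |

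In the -10 row the listed model also produces a spurious baseline trend of +0.60 to +0.65 per session. If a slope change of -1 comes with a +5 offset, the coefficient turns positive, at about +0.3 to +0.5 depending on whether the slope counts from the last baseline or the first intervention session.

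**Sensitivity to the assumptions.**
- With a between-participant slope SD of 1 point per session, the -5 and -10 shifts are flagged in 30-31% and 82-83% of trials.
- With total SD 20 and no random slopes, they are flagged in 15-16% and 44-47%.
- With a slope SD of 0.5 or 1 on the interaction, power for the -1 slope change is 9-12%, against 33-52% with a phase term.

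**Alternative coding.** Suppose the session count in the interaction restarts at the phase change, still without a phase term. With zero at the last baseline session, a jump-free slope change of -1 is recovered as -1.00, and a -10 level shift leaks in as +0.2 to +0.4. With zero at the first intervention session, these become -0.92 and about +0.8. The leak has the opposite sign to that under the running number.

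**The case against.** The strongest reply is that the article does not say how session is coded inside the interaction, but does say what the coefficient means. A broken-stick model (time plus sessions since the phase change) also has two fixed effects, and its second coefficient is the change in trend when there is no jump. On that reading nothing is hidden: power for a -1 slope change is 40-54%, about that of the model with a phase term. This stands in part. The count of "two fixed effects and one random effect" fits either coding and does not settle the matter. But the text calls the predictor the session number and equates it with time, and a reader would fit the running number. Under the restarted clock, a level shift still enters the coefficient.

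Second, the percentages are illustrative. The SD of 10 is not in the article, the plan allows random slopes, and the outcome is scaled to each participant's own baseline mean, so a random intercept with ICC 0.18 only roughly represents it. This also stands. The direction of the distortion remains.

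Third, a reader might infer that the trial would falsely claim efficacy. The documents do not support that. Under no effect at all the test rejects at 5%, and a real level improvement would itself be a benefit under the stated hypothesis. The fault is in the meaning and power of the coefficient.

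A reader might also infer from the option of additive models that no interaction coefficient would remain to be tested. That is not established, since an additive mixed model can carry a parametric interaction beside a smooth. The option does not, however, supply the missing phase term.

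**Conclusion.** The point holds, conditionally in its size. As written, the primary coefficient does not have the meaning the plan gives it. Under the running session number it recovers about 22-24% of a jump-free slope change, and it turns a pure level shift into an apparent trend change. The rates of 44-47% (shift of -5) and 95-96% (shift of -10) rest on an assumed total SD of 10 and a random intercept, and they are lower with random slopes or a larger SD. Under a restarted clock the loss of slope largely disappears and only the leakage of a level shift remains. Under either reading the wording needs correction, because neither the coding nor a phase term is stated. The sample-size arithmetic follows from its own inputs and is not at fault.

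**What to change.** State the primary model as: outcome = session + phase + phase × (sessions since the phase change), with random effects where estimable and AR(1) errors. Say whether the first intervention session counts as 0 or 1, because the phase term is the level difference at the zero point. State that the interaction is the slope change and the phase term the level change, and report both. Name the linear version as primary and the additive model as a sensitivity analysis. Use the same terms wherever the model is reused. The phase term will also carry any shift caused by testing straight after training, so it should be interpreted with that in mind.

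The cost is precision. At SD 10 the standard error of the slope change rises from about 0.29 to 0.47 (AR(1) of 0), or from 0.31 to 0.57 (AR(1) of 0.3), relative to the running-number model. By the protocol's own method, a fourth numerator df gives 85.8 observations: 85.8 × 3.79 / 16.5 = 19.7, and 19.7 / 0.9 = 21.9, so about 22 participants rather than 20. Restating the power or sample-size statement for the corrected model is enough; enrolling more is not required by this point. The conduct of sessions does not change.
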